### Power calculations

A sample of 600 would allow a mean score of 86.4 to be estimated with a 95% CI of 84.2 to 88.6 (mean and SD based on Foo *et al*^8^) for the primary outcome measure (the emotional role subscale of Short Form 36 (SF-36)). With just over 1000 babies born each year with CL/P, the total population available to recruit from over a 2-year period is approximately 7000 (1000 individuals born with cleft each year for ages 18–23—totalling 6000—plus an additional year of recruitment to include young adults who turn 18 during the first year of recruitment). The recruitment rate for a comparable study run by the same team and involving younger children was 75%^9^; therefore, recruiting 600 is achievable. Nevertheless, we propose to over-recruit by 40 (total sample size 640) as contingency for missing data.

To achieve a sample size of 640, we aim to recruit from across the UK’s cleft teams. Some serve a larger population than others, so it is likely that we may recruit more from some sites than others. Our work with young people to date suggests that they would be willing to attend this research clinic. We aim to recruit participants across all groups to ensure that the study sample reflects the general population in terms of ethnicity, socioeconomic status, gender and cleft subtypes. Recruitment will be facilitated through targeted dissemination of study information via general medical practices, dental practices and community organisations serving diverse ethnic groups. Regular evaluation of those recruited will ensure the sample is representative of target population in ethnicity, biological sex, socioeconomic status and geographic location to minimise the risk of selection bias.

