### Data analyses

Descriptive statistics will be used to summarise the exposures (ethnicity, sex, gender, socioeconomic status and geographical location) using frequencies and percentages. For the numerical outcomes, central tendency and variation will be summarised by means and SD or medians and IQRs as appropriate. Categorical outcomes will be summarised by frequencies and percentages.

Regression models will be used to assess associations between the exposures and the primary outcome. Secondary analysis will be based on regression models for each of the other outcomes separately. Linear, logistic, ordinal logistic or Poisson regression will be used to model associations for continuous, binary, ordinal or discrete outcomes, respectively; continuous outcomes will be transformed before analysis if model residuals are skewed.

Directed acyclic graphs will be used to conceptualise associations between variables to enable an appropriate set of confounders to be selected for modelling each exposure-outcome association; age and the other exposures will be considered as potential confounders as well as health literacy and dispositional optimism. All models will be fitted before and after adjustment for appropriate confounders. A sensitivity analysis will be undertaken, whereby all unadjusted models will be repeated, restricting to only those with full confounder information available. This will confirm whether any changes after adjustment are due to missing data or the confounding variables themselves.

Potential cleft centre-level variation for each outcome will be identified through estimation of variance partition coefficients from multilevel models with centre treated as a random effect, adjusting for appropriate fixed effects (eg, age and sex). Any outcomes displaying centre-level variation will be modelled using multilevel rather than single-level models.

Potential effect modification through cleft subtype and/or syndromic status will be tested through inclusion of interaction terms in models; if the exposure-outcome association differs according to the categories of cleft subtype/syndromic status, category-specific regression estimates will be presented.

The economic impact of a cleft diagnosis will be collected through the self-report questionnaire and will be analysed to determine variation in resource use within the sample.

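### Whether subtype- and syndrome-specific associations are shown depends on interaction tests the study was not sized for; for the primary outcome they should be reported whatever the test shows

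*Protocol article*

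**What the plan says.** Under Data analyses, the protocol article states: "Potential effect modification through cleft subtype and/or syndromic status will be tested through inclusion of interaction terms in models". The same sentence continues that, where the association is found to differ between those categories, "category-specific regression estimates will be presented". The rule concerns exposure associations within categories of subtype or syndromic status, not the mean outcome in each category. The article gives no criterion for deciding that an association differs.

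Under Power calculations, the only basis for the sample size is the precision of a single mean: "A sample of 600 would allow a mean score of 86.4 to be estimated with a 95% CI of 84.2 to 88.6". The team will then "over-recruit by 40 (total sample size 640) as contingency for missing data". No between-group contrast or interaction is used to size the study.

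The exposures listed under Data analyses are ethnicity, sex, gender, socioeconomic status and geographical location. The primary research question in the Introduction names four: ethnicity, biological sex, socioeconomic status and geographic location.

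**The concern.** When a result is displayed only after passing a test, the test decides what readers see. If the test has low power, two things follow. Real differences of moderate size are mostly not displayed, and those that are displayed passed partly because chance pushed the estimate upwards, so they are too large on average.

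This matters because the programme aims to explore and explain variation. All cleft subtypes, with and without syndromic diagnoses, are eligible. A reader who finds no category-specific estimates for an exposure may take the association to be the same across categories, when the data could not have shown otherwise.

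**Working it through.** **Inputs from the protocol.** n = 600, mean 86.4, 95% CI 84.2 to 88.6 (Power calculations).

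**Assumptions not in the protocol.** A two-sided 5% criterion, normal approximation, binary exposure and binary modifier, and the category shares shown in the table. Exposures or modifiers with more categories would generally thin the cells further.

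**Step 1: reproduce the stated interval.** The half-width is (88.6 − 84.2)/2 = 2.2. The SD is not printed; solving 1.96 × SD/√600 = 2.2 gives SD = 27.5 (26.9 to 28.1 allowing for rounding). Putting 27.5 back gives 86.4 ± 2.2, that is 84.2 to 88.6. This shows internal consistency only, since the SD came from the interval.

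**Step 2: detectable main contrast.** For two groups of 300, SE = 27.5 × √(1/300 + 1/300) = 2.245. At 80% power the detectable difference is (1.96 + 0.842) × 2.245 = 6.3 points (0.23 SD).

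**Step 3: the same size as an interaction.** With exposure share pe and modifier share pm, SE = SD/√(n × pe(1 − pe) × pm(1 − pm)). In the best layout (both 50%), SE = 27.5/√(600 × 0.25 × 0.25) = 4.49, twice the main-contrast SE. Power = Φ(6.29/4.49 − 1.96) + Φ(−6.29/4.49 − 1.96) = 0.29. Because the SE ratio is exactly 2, this 29% depends on neither the SD nor n.

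**Step 4: overstatement.** This is the mean absolute estimate among results passing the 5% criterion, divided by the true 6.29 (1,000,000 normal draws). As a check in the best layout, with 6.29/4.49 = 1.401 and ignoring the far tail: (1.401 + φ(0.559)/Φ(−0.559))/1.401 = (1.401 + 0.341/0.288)/1.401 = 1.8.

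| Exposure share | Modifier share | Interaction SE | Detectable at 80% power | Power at 6.3 points | Mean overstatement if passed |
|---|---|---|---|---|---|
| 50% | 50% | 4.49 | 12.6 | 29% | 1.8-fold |
| 50% | 25% | 5.19 | 14.5 | 23% | 2.1-fold |
| 50% | 10% | 7.48 | 21.0 | 13% | 2.9-fold |
| 20% | 10% | 9.36 | 26.2 | 10% | 3.6-fold |

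With n = 640 the best-layout detectable interaction falls only to 12.2 points.

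**Step 5: a large interaction.** At 13.75 points (0.5 SD), the best layout has 87% power and 1.08-fold overstatement. With a 10% modifier share (exposure 50%) the figures are 45% and 1.48-fold.

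**Step 6: chance findings on the primary outcome.** If every exposure is crossed with both modifiers, 5 × 2 = 10 tests. With no true interactions and independent tests, 1 − 0.95^10 = 0.40 is the chance of at least one signal. With the four exposures of the primary question, 1 − 0.95^8 = 0.34. The independence assumption is doubtful, for example for sex and gender, so these are rough guides.

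**The case against.** The strongest reply is that the article states neither a p-value nor that category-specific estimates appear *only* after a positive test. It also does not say that interaction estimates or their intervals will be withheld. A condensed article may leave the criterion and the handling of null interactions to an analysis plan. Testing for interaction before showing stratum estimates is a common restraint on over-reading subgroups. Effect modification is subsidiary here, and the main associations are modelled regardless. Category shares and interaction sizes are assumed, and displaying every pair does not lower the number of chance interactions.

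Much of this stands. The missing threshold is not a fault in itself, the power figures are illustrative, and multiplicity is not cured by wider display. What does not fall is the conditional wording: any data-dependent criterion leaves presentation dependent on the result, and a later choice of threshold would not remove the selection.

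A reader might infer that every difference shown will be exaggerated or false. The documents do not support that. Overstatement is an average over repeated studies, and it is slight for a large interaction in a balanced layout. A reader might also infer that the plan treats a null test as proof of no difference; it draws no such conclusion. The risk is that readers of the results will.

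**Conclusion.** The point holds in limited form. The plan makes presentation of category-specific associations conditional on an interaction result, and the study is sized only for one overall mean. Under a 5% criterion, an interaction as large as the detectable 50/50 main contrast has at most about 29% power, and less in every unbalanced split tried. Moderate real differences would usually not trigger presentation. Those that do would on average be overstated by about 1.8- to 2.9-fold with a 50% exposure share and a modifier share between 50% and 10%, and some would be due to chance.

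The conclusion rests on the assumed criterion, category shares and interaction size. The points scale rests on the SD implied by the stated interval. It does not extend to large interactions in well-filled categories, and it is not a claim that any particular displayed difference is wrong.

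**What to change.** For the primary outcome, replace the conditional clause in Data analyses. List the exposure-by-modifier pairs in advance. For each pair, report the interaction estimate with its 95% CI and the category-specific estimates, whatever the test result, labelled exploratory. State how sparse categories will be collapsed or flagged, and that a non-significant interaction will not be interpreted as no difference.

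The cost is a rewritten sentence and a longer table, which may go in a supplement, with some wide intervals in small categories. Recruitment and data collection are unaffected. The change removes selective presentation on the primary outcome but does not reduce the number of chance interactions, which is why the exploratory label is needed.

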### Data deposition and curation

Data are held on a combination of restricted access network folders and the University of Bristol (UoB) servers. All of the above rely on Windows authentication administered by the UoB IT Services and have been approved for storage of this type of data. Data generated by the Cleft@18–23 study will be maintained on secure servers at UoB, which are backed up on a regular basis.

Primary source material (eg, questionnaires, case report forms and consent forms) will be preserved as electronic (scanned) and hard (paper) copies where practicable. Paper copies of consent forms, case report forms and questionnaires will be stored in locked cabinets in restricted access offices until they are digitised. Once digitised, these documents will be securely destroyed in line with institutional policies. Data transfers between systems and collaborators will use encrypted methods (eg, password-protected ZIP files and Advanced Encryption Standard-256 encryption) to minimise the risk of breaches.

At the end of the study, all data will be stored on the UoB Research Data Storage Facility. Where participants have consented, their data will be stored indefinitely and made available to external researchers following the process, which will be detailed in a data access policy. This will include the need for submission of a proposal for use of the data, ethical approval for the analysis planned and approval from the data custodians. We will follow the standards and policies set out by UoB. Further information on data security can be found here: http://www.bristol.ac.uk/infosec/policies/.

### Patient and public involvement

Focus groups with members of the patient community, specifically 10 young adults aged between 16 and 20 years informed the development of the funding application. A PPI group comprising young adults aged 18–30 years born with a CL/P has now been established for the study and this group has informed key elements in the writing of the protocol and development of recruitment resources. We have an ongoing process for recruitment to the PPI group to ensure that we have sufficient PPI representation throughout the study.

PPI has informed:

the acceptability of the research;design of the research.

PPI will have an ongoing role in providing input to:

recruitmentmanagement of the research;undertaking the research;analysis of results;dissemination of findings.

### Ethics and dissemination

Ethical approval for Cleft@18–23 was provided by the South West-Frenchay Research Ethics Committee on 26 November 2024 (REC reference: 24/SW/0128). Subsequent Health Research Authority and Health Care Research Wales approval for the study was also given on the same day. Cleft@18–23 is sponsored by University Hospitals Bristol and Weston NHS Foundation Trust. Informed consent is required for participation.

Findings from Cleft@18–23 will be disseminated through peer-reviewed publications and through national and international conference presentations, both oral and poster. To promote open research and support rapid dissemination, the study team and collaborators using the Cleft@18–23 resource for their research may also publish preprints of their papers using preprint servers such as Medrxiv or Biorxiv subject to their target journal guidance. Papers published will be promoted through the Cleft@18–23 website (https://www.bristol.ac.uk/cleft18-23), newsletters and through social media (Bluesky: @cleft1823study.bsky.social; Facebook: cleft1823; Instagram: @cleft1823study; LinkedIn: Cleft1823study).
